## 1. INTRODUCTION

In Germany there are about 15,000 newly diagnosed neoplasms of the pancreas each year.[5] Exact numbers for benign or borderline lesions do not exist. In 2011 approximately 11,800 partial resections of the pancreas were performed in German hospitals.[6]

Pancreatic surgery is complex from a diagnostic, surgical and perioperative point of view. Centralization of pancreatic surgery in specialized institutions has led to acceptable mortality rates below 5%.[7-9] Moreover, standardization of surgical and perioperative care in these centers of expertise is a prerequisite for low morbidity rates.[7]

Postoperative pancreatic fistula (POPF) still represents the most common postoperative morbidity in pancreatic surgery and can profoundly affect patient recovery and outcome. The incidence of POPF reported in the literature varies widely with overall rates between 0% and 24%.[10] After pancreaticoduodenectomy (PD) POPF rates range from 10% to 15% in different studies, and usually occur at a higher rate of about 10% to 30% after DP respectively.[11] In a large multicenter RCT conducted by the SDGC comparing stapler vs. hand-sewn closure of the pancreas after DP, the overall POPF rate was 30% in 352 analyzed patients, coinciding well with the rates in the literature.[12]

In-hospital mortality due to POPF or subsequent complications occur in up to 14%.[13] reaching up to 33% in high-risk subgroups.[14]

Pancreatic surgeons still lack an effective strategy to reduce the rates of POPF. Therefore, further research on the prevention of POPF is obligatory.

### 1.1 SCIENTIFIC BACKGROUND

In current routine practice, after DP the pancreatic remnant is usually closed by either the use of a stapler or by hand-suture with conventional surgical sutures without any further measures. Several surgical techniques and technical modifications have been proposed in an attempt to reduce fistula rates in pancreatic surgery.[15] For instance, different types of fibrin sealants have been evaluated in their potential to reduce the occurrence of POPF, but none of them has been proven effective so far.[16, 17] A recent systematic review and meta-analysis of Orci et al. [18] concluded that “fibrin sealants cannot be recommended for routine clinical use in the setting of pancreatic surgery”. Also, mesh reinforcements of the pancreaticojejunal anastomosis have provided no significant benefit in the reduction of POPF.[19]

Compared to fibrin sealants, the medical glue 2-OCA is also easily applicable to the resection surface and will not be degraded by aggressive pancreatic enzymes due to its long-lasting tissue bonds. Cyanoacrylate is an acrylic resin that rapidly polymerizes in the

|      |                      |            |
|------|----------------------|------------|
| BOND | Protocol version 3.2 | 12.11.2014 |
|------|----------------------|------------|

presence of water, forming, long, strong bonds that join surfaces together. The compound 2-OCA is a nontoxic bacteriostatic medical glue that has been widely used to approximate skin edges.[20] Recently, ETHICON™ OMNEX™ a new surgical sealant, consisting of a blend of 2-OCA and butyl-cyanoacrylate (BLCA), has been approved by the FDA and has been CE-certified for the intracorporal use in vascular surgery.

In 2013, Barakat et al. [21] have published their first results on the topical application of 2-OCA to the pancreaticojejunal anastomosis after PD. They reported a highly significant reduction of POPF for the 2-OCA group compared to patients without 2-OCA application. The rate of POPF in the 2-OCA group was 3.5% compared to 36% in the group without 2-OCA application. Currently, no further evidence on the application of 2-OCA in pancreatic surgery is available in the literature.

## **1.2 TRIAL RATIONALE**

Based on the results of Barakat et al. [21], topical 2-OCA application promises a substantial benefit in the prevention of POPF. Currently, there are only data available on the topical application to the pancreaticojejunal anastomosis after PD. Therefore, we intend to expand this promising technique to further pancreatic interventions. DP shows even higher rates of POPF compared to PD, thus, there may be a larger benefit for prevention of POPF in this indication.

Based on these facts, we conduct this trial in a proof-of-concept design to further develop the technique and to evaluate safety and preliminary efficacy in these indications.

## **1.3 OBJECTIVES**

The main objective of this study is to evaluate the safety of a 2-OCA application to the pancreatic remnant after distal pancreatectomy. Therefore all serious adverse events will be closely monitored. If the intervention proves to be safe under these conditions, a multicenter RCT will be planned to evaluate the efficacy of this new and promising technique.

As primary efficacy parameter, the rate of POPF will be assessed.

## **1.4 TRIAL DESIGN**

BOND is a monocenter open label prospective proof of concept and safety trial in a single arm study design at the development stage (according to the IDEAL recommendations [4])

## **1.5 TRIAL DURATION AND SCHEDULE**

|      |                      |            |
|------|----------------------|------------|
| BOND | Protocol version 3.2 | 12.11.2014 |
|------|----------------------|------------|

The duration of the trial for each patient is planned to be 3 months. The duration of the overall trial is expected to be 2 years, including prearrangement and analysis.

## 2. TRIAL CONDUCT

### 2.1 ELIGIBILITY CRITERIA

#### Key inclusion criteria:

- Patients scheduled for elective distal pancreatic resection (DP)
- $\geq 18$  years of age
- Written informed consent

#### Key exclusion criteria:

- Haemoglobin  $< 10$  g/dl
- Bilirubin  $> 3$  times ULN
- AST or ALT  $> 4$  ULN
- INR  $> 1.7$
- Creatinine clearance  $< 30$  ml/min (estimated by Cockcroft-Gault)
- Serious cardiovascular disease (e.g. myocardial infarction in the last 12 months, congestive heart failure NYHA III/IV, unstable angina pectoris)
- Liver cirrhosis (of any Child-Pugh grade)
- ASA score  $> III$
- Immunosuppressive therapy (cortison  $\geq 40$  mg/d or equivalent; azathioprin)
- Pregnancy or lactation
- Drug trial participation within 30 days before screening visit
- Understanding or language problems
- Inability to comply with study and/or follow-up procedures
- Allergy or known intolerance to 2-OCA, butyl-lactoyl cyanoacrylate or formaldehyde
- Any condition which could result in an undue risk for the patient in the opinion of the investigator

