| Key inclusion and exclusion criteria | Key inclusion criteria: 
 
• Patients scheduled for elective distal pancreatic resection (DP)
 
• ≥ 18 years of age
 
• Written informed consent
 
 Key exclusion criteria: 
 
• Haemoglobin < 10 g/dl
 
• Bilirubin > 3 times ULN
 
• AST or ALT > 4 ULN
 
• INR > 1.7
 
• Creatinine clearance < 30 ml/min (estimated by Cockcroft-Gault)
 
• Serious cardiovascular disease (e.g. myocardial infarction in the last 12 months, congestive heart failure NYHA III/IV, unstable angina pectoris)
 
• Liver cirrhosis (of any Child-Pugh grade)
 
• ASA score > III
 
• Immunosuppressive therapy (cortison ≥ 40 mg/d or equivalent; azathioprin)
 
• Pregnancy or lactation
 
• Drug trial participation within 30 days before screening visit
 
• Understanding or language problems
 
• Inability to comply with study and/or follow-up procedures
 
• Allergy or known intolerance to 2-octyl cyanoacrylate, butyl-lactoyl-cyanoacrylate or formaldehyde
 
• Any condition which could result in an undue risk for the patient in the opinion of the investigator
 
 |

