## **2.2 INTERVENTION(S)**

### **2.2.1 Investigational Device**

The name of the investigational device is ETHICON™ OMNEX™ Surgical Sealant. The device is manufactured for ETHICON™ by Closure Medical Corp., Raleigh, North Carolina, 27616. ETHICON™ is a division of Johnson & Johnson Medical Limited. Distribution in Germany is done by Johnson & Johnson Wound Management, [name].

ETHICON™ OMNEX™ Surgical Sealant is a synthetic tissue sealant consisting of a blend of two monomers, 2-OCA and butyl-lactoyl-cyanoacrylate (see "Instructions for Use" in the Appendix). The liquid formulation is contained in a crushable glass ampoule, which is housed in a single-use delivery device. The formulation is passed through a porous disc containing an initiator, mixed in a chamber, and delivered through a cannula. When polymerization is complete, a film is formed that mechanically interlocks the tissue and/or non-biological materials (i.e. synthetic graft sutures, staples, clips) and creates a flexible physical seal, independent of the body's clotting mechanism. ETHICON™ OMNEX™ Surgical Sealant begins to polymerize immediately on mixing with the initiator and forms a physical seal within 2 minutes after application. ETHICON™ OMNEX™ Surgical Sealant has been formulated to provide a strong physical seal that remains in place beyond the time required for natural healing, and eventually degrades via hydrolytic chain scission (over approximately 36 months), breaking down into smaller absorbable fragments.

The sterile, non-pyrogenic device is provided as a packaged single-use applicator and stored at room temperature.

ETHICON™ OMNEX™ is a CE marked and certified device. It conforms to the essential requirements of the Medical Device Directive 93/42/EEG and was tested in conformity to the ISO 10993 series for biocompatibility of a long-term implantable medical device.

|      |                      |            |
|------|----------------------|------------|
| BOND | Protocol version 3.2 | 12.11.2014 |
|------|----------------------|------------|

Further information about the investigational device including a summary of preclinical and clinical testing can be found in the investigator's brochure ("Handbuch des klinischen Prüfers"), provided by the SDGC.

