## **2.2.2 Description of trial interventions**

2-OCA in DP: After routine resection of the pancreatic tail and/or body the remnant will be closed according to local standards [22] by direct suture of the pancreatic duct with a non-reabsorbable surgical suture (e.g. Novafil 4-0) and closure of the pancreatic tissue with absorbable sutures (e.g. PDS 5-0) in fish-mouth technique. After the conventional closure, a thin layer of the 2-OCA surgical sealant will be applied to the sutured surface of the pancreatic remnant (not exceeding 4 ampoules). The surrounding area will be covered with sterile surgical gauzes to avoid contact of the sealant to other tissue not intended to get in contact with the sealant. Before application, the surface of the pancreatic remnant will be patted dry with a sterile gauze, to assure direct contact of the sealant to the tissue as described in the directions for use of the product. No additional covering of the pancreatic remnant will be conducted. Additional sutures of the cut surface for reasons of hemostasis will be allowed. After polymerization of at least 2-3 minutes the operation will be continued in a routine manner.[22] Perioperative treatment will not be changed by the trial intervention and will be conducted according to local standards.

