## CONTRAINDICATIONS

- Do not use on patients with known hypersensitivity to cyanoacrylate or formaldehyde.
- Not for intravascular use.

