#### **VIII. POTENTIAL ADVERSE EFFECTS OF THE DEVICE ON HEALTH**

Below is a list of the potential adverse effects (e.g., complications) associated with the use of this class of surgical sealants:

- Hypersensitivity reaction such as swelling or edema at the application site
- Application of the sealant to tissue not targeted for the procedure

|      |                      |            |
|------|----------------------|------------|
| BOND | Protocol version 3.2 | 12.11.2014 |
|------|----------------------|------------|

- Failure of the sealant to adhere to the tissue
- Thrombosis and thromboembolism

Below is a list of the potential adverse effects (e.g., complications) associated with cardiac and vascular procedures:

- Adhesions
- Anastomotic pseudoaneurysm
- Aortic insufficiency
- Cardiac tamponade
- Cerebral emboli
- Coagulopathy
- Death or irreversible morbidity
- Dissection
- Edema
- Erythema
- Hematoma
- Hemorrhage
- Infection
- Injury to normal vessels or tissue
- Ischemia
- Lymphocle/lymph fistula
- Myocardial infarction
- Neurological deficits
- Organ system dysfunction/failure
- Pain
- Paraplegia
- Pleural effusion
- Pulmonary emboli
- Renal dysfunction/failure
- Stroke or cerebral infarction
- Thrombosis
- Vasospasm
- Vessel rupture and hemorrhage

For the specific adverse events that occurred in the clinical studies, please see Section X below.

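### The allergy exclusion names only the device's two monomers and formaldehyde, while the appended contraindication says cyanoacrylate without that limit (minor patient-safety alignment)

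*Protocol*

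**What the plan says.** The exclusion list in Protocol 2.1 contains the item "Allergy or known intolerance to 2-OCA, butyl-lactoyl cyanoacrylate or formaldehyde". The synopsis has the same item with the first compound spelled out: "Allergy or known intolerance to 2-octyl cyanoacrylate, butyl-lactoyl-cyanoacrylate or formaldehyde". The last item of the list is a general one: "Any condition which could result in an undue risk for the patient in the opinion of the investigator".

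Section 2.2.1 describes the device as "consisting of a blend of two monomers, 2-OCA and butyl-lactoyl-cyanoacrylate", so the exclusion names both cyanoacrylates that the device contains.

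The manufacturer's instructions for use are Appendix I of the protocol. Their contraindications state "Do not use on patients with known hypersensitivity to cyanoacrylate or formaldehyde". Section III of the FDA summary in Appendix II repeats this. The same summary lists the exclusion criteria of the multicenter pivotal study, and these also refer to cyanoacrylate and formaldehyde with no compound named.

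**The concern.** An allergy criterion would be expected to reach at least as far as the manufacturer's instruction not to use the product. On substance this one does not: it lists two particular cyanoacrylates, while the instruction uses the general word. The gap concerns one kind of patient, someone with a documented reaction to another, identified cyanoacrylate.

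The main objective in section 1.3 is safety, and section VIII of Appendix II lists among the potential adverse effects of this class of sealants "Hypersensitivity reaction such as swelling or edema at the application site". Exposure is also hard to reverse. Section 2.2.2 allows up to 4 ampoules, section 2.2.1 gives a degradation time of about 36 months, and the precautions in Appendix I warn that peeling the set sealant could damage tissue. It is therefore better for a firm criterion to settle such a case than for it to depend on individual judgement.

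**Working it through.** No arithmetic applies. The check compares the wording of the relevant texts on two dimensions and then asks which rule decides the case.

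| Text | Reaction | Substance |
|---|---|---|
| Protocol 2.1 and synopsis | allergy or known intolerance | 2-OCA, butyl-lactoyl cyanoacrylate, formaldehyde |
| Appendix I, Contraindications | known hypersensitivity | cyanoacrylate (no compound named), formaldehyde |
| Appendix II, section III | known hypersensitivity | cyanoacrylate (no compound named), formaldehyde |
| Appendix II, pivotal study exclusions | known hypersensitivity | cyanoacrylate (no compound named), formaldehyde |

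1. **Reaction.** The protocol is the wider text, because it also covers intolerance. There is no shortfall here.

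2. **Substance.** The protocol is the narrower text. It lists two cyanoacrylates, and the other three entries name none. The instructions for use name both monomers in their device description but use the general word in the contraindication. Reading that word as wider than the two monomers is the natural reading, though the label does not say *any* cyanoacrylate.

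3. **Which rule decides the case.** Take a patient whose documented reaction was to an identified cyanoacrylate other than 2-OCA or butyl-lactoyl cyanoacrylate. The named item does not apply. The only other item in the list that could apply is the undue-risk item, and that is discretionary.

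4. **Whether the label is brought in as an eligibility rule.** Section 2.1 does not mention the contraindications. Section 2.2.1 points to the instructions for use when describing the product. Section 2.2.2 invokes them for drying the surface, "to assure direct contact of the sealant to the tissue as described in the directions for use of the product". Section 2.2.4 refers to handling instructions in the brochure. No text shown turns the contraindications into an exclusion criterion.

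5. **How many patients.** The synopsis plans for 50 assessed and 35 allocated. The documents give no frequency for reactions to other cyanoacrylates, so no expected count can be derived from them.

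**The case against.** The strongest reply is that there is no conflict. The device contains two cyanoacrylates, the exclusion names both and adds formaldehyde, and the label's general word may simply be shorthand for those two. The pivotal study uses the same unspecific word; it favours the wider reading without settling it. This stands as a limit: the mismatch is one of plain wording and not a proven contradiction.

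The second reply is that other safeguards exist. The contraindication is bound into the protocol, section 2.2.4 obliges all investigators to read the protocol and the brochure and provides training, and the visit table has eligibility checked at screening and again on the day of surgery. Most of this stands. A reader might infer that the undue-risk item is the sole protection, but that is true only within the eligibility list. The second eligibility check adds little on this point, because it applies the same criteria. The brochure is not shown and may repeat the contraindication.

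A reader might also infer that a cyanoacrylate allergy of unknown product slips through. The documents do not support this. Section 1.1 says "The compound 2-OCA is a nontoxic bacteriostatic medical glue that has been widely used to approximate skin edges", so the unknown product could well have been 2-OCA, and such a patient would reasonably be treated as excluded already.

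Finally, no text addresses cross-reactivity. That a reaction to another cyanoacrylate predicts a reaction to this device cannot be shown from the documents; the case for excluding such patients rests on the label's wording.

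**Conclusion.** The point holds as a minor patient-safety alignment. On plain wording, the named criterion is narrower on substance than the contraindication appended to the same protocol and than the exclusion used in the device's pivotal trial. A documented reaction to a different, identified cyanoacrylate is therefore left to the investigator's discretion within the eligibility list.

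The size is very small and possibly zero patients. That is a judgement, since the documents give no frequency; any percentage put on it would be a guess, and would describe candidates assessed before the safeguards act. Enrolment of such a patient is unlikely. The conclusion assumes that the label's word is not confined to the two monomers. It does not extend to a claim that contraindicated patients will be treated or that harm is to be expected. Sample size, analysis and the interpretation of results are untouched.

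**What to change.** In section 2.1 and the synopsis, reword the item as: *Allergy or known intolerance to any cyanoacrylate (including 2-OCA and butyl-lactoyl cyanoacrylate) or formaldehyde*. This keeps the protocol's wider reaction wording and brings the substance into line with the plain wording of Appendices I and II. It also makes the unknown-product case explicit.

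The cost is a few words in two places and a negligible loss of eligible patients. The planned 35 patients and the descriptive analysis stay as they are.

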#### 2.1.1 Number of patients and trial centers

BOND will be conducted as a monocenter proof-of-concept and safety trial, therefore no actual sample size calculation was performed. A total of 35 patients is planned to be included into the trial. From our previous RCT on DP and from a review of the literature, there is good evidence that the rate of POPF after conventional DP is 30%. [12] Thus, we would expect the occurrence of about 10 cases of POPF without application of the sealant which should be reduced by the application of the 2-OCA sealant. Therefore, a number of 35 was judged sufficient for a preliminary evaluation of safety and applicability by the investigators in this early phase of the new technique. BOND will be conducted as a monocenter trial at the Department of General, Visceral, and Transplantation Surgery at the University of Heidelberg, Heidelberg, Germany. If the trial intervention proves to be safe, a multicenter RCT is planned with a sample size calculation based on the preliminary efficacy results (frequency of POPF).

|      |                      |            |
|------|----------------------|------------|
| BOND | Protocol version 3.2 | 12.11.2014 |
|------|----------------------|------------|

### **2.1.2 Criteria for withdrawal of patients**

Patients are free to leave the trial at any time and without giving reasons for their decision. Subjects may be withdrawn from the trial for the following reasons: (a) At their own request or (b) If, in the investigator's opinion, continuation of the trial would be detrimental to the subject's well-being. In case of (b), the reason for withdrawal must be recorded in the CRF and in the patient's medical records.

Patients that were included into the trial but the designated intervention could not be performed due to any reason (e.g. DP was not feasible upon abdominal exploration) will be replaced by consecutive patients until the planned sample size is reached.

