## **4. STATISTICAL PROCEDURES**

### **4.1 SAMPLE SIZE CALCULATION**

A total of 35 patients will be recruited to the trial and treated by the application of the 2-OCA surgical sealant to the surface of the pancreatic remnant after DP. This sample size is judged sufficient for the evaluation of safety and applicability in this setting. If the trial proves safety of the intervention, a multicenter efficacy RCT will be conducted consecutively.

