### **4.2 ANALYSIS VARIABLES AND STATISTICAL METHODS**

All patients treated with the trial intervention will be considered in the final analysis.

The empirical distribution of all endpoints will be calculated, including mean, standard deviation and quartiles in case of continuous variables and scores, and with absolute and relative frequencies in case of categorical data. 95% confidence intervals will be calculated. Whenever appropriate, statistical graphics will be used to visualize the findings.

Missing data will be minimized by consequent documentation and all other reasonable methods. No interpolation of missing data will be performed.

(Serious) adverse events will be summarized using descriptive statistics. The adverse events will be categorized as surgical, cardiovascular, pulmonary, urinary and other complications. Furthermore, it will be defined if events were device-related or not. Device-related and not device-related (serious) adverse events will be reported separately. Proportions and frequencies of adverse events will be presented. Specific focus will be placed on potential device-related adverse events.

Because the BOND-Trial is designed as a proof-of-concept trial no formal analyses will be conducted. In case of safety and feasibility, the results will serve as a basis for sample size calculation (set into relation to the results from previous RCTs) for a succeeding randomized controlled trial.

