#### Unanticipated Serious Adverse Device Effect (USADE)

An unanticipated serious adverse device effect (USADE) is a serious adverse device effect which by its nature, incidence, severity or outcome has not been identified in the current version of the risk analysis report, as contained in the investigator's brochure ("Handbuch des klinischen Prüfers").

In contrast, an anticipated serious adverse device effect (ASADE) is an effect which by its nature, incidence, severity or outcome has been identified in the risk analysis report.

All adverse events occurring during the period between the application of the medical device and the last follow-up visit must be documented on an "Adverse Event Form" in the CRF. All untoward medical occurrences appearing prior to the application of the medical device will be recorded as medical history.

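### The replacement rule covers any reason for not performing the intervention, so a patient with a completed resection but no sealant drops out of the denominator for applicability

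*Protocol*

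**What the plan says.** Section 2.1.2 of the protocol sets the replacement rule. It applies to "Patients that were included into the trial but the designated intervention could not be performed due to any reason" and continues: "e.g. DP was not feasible upon abdominal exploration) will be replaced by consecutive patients until the planned sample size is reached". The infeasible resection is an example, not a limit. The section requires a recorded reason when the investigator withdraws a patient. It states no such requirement for a replaced patient.

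Section 2.2.2 describes the intervention as sealant applied to the remnant after routine resection and suture closure. A patient with resection and closure but no sealant has therefore not had the intervention.

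Section 4.2 defines the analysis population in one sentence: "All patients treated with the trial intervention will be considered in the final analysis". It names no population of included patients or of intended or attempted applications.

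The purpose of the sample is given twice. Section 2.1.1 says that "a number of 35 was judged sufficient for a preliminary evaluation of safety and applicability", and section 4.1 repeats: "This sample size is judged sufficient for the evaluation of safety and applicability in this setting". Section 4.2 adds a condition for the next step: "In case of safety and feasibility, the results will serve as a basis for sample size calculation".

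Three other provisions bear on the point:
- Section 2.4.1 (Visit 2) has the CRF describe the application and any problems with it.
- Section 6 has each use of the device logged per patient, together with product deficiencies.
- Section 5.2 starts adverse event documentation at application: "All untoward medical occurrences appearing prior to the application of the medical device will be recorded as medical history".

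**The concern.** Replacing a patient who turns out not to have a DP is unobjectionable, because that patient was never a candidate for the sealant. The rule makes no distinction between this case and a completed resection whose remnant could not be sealed, for example because the surface could not be kept dry or the applicator failed. That second patient is the one who tells the team whether the technique can be applied.

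Under sections 2.1.2 and 4.2 together, this patient is replaced and is not in the named analysis population. Any statement about applicability then rests on patients selected because application succeeded. What is at stake is the feasibility half of the condition that section 4.2 sets for using the results to plan the randomised trial. If the randomised trial is analysed as allocated, patients who cannot be sealed will stay in its experimental arm, and its planners would need to know how many to expect.

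**Working it through.** **The plan's own figure.** Section 2.1.1 expects about 10 fistulas in 35 patients at a 30% rate without sealant: 35 × 0.30 = 10.5, which agrees. The number 35 has no formula behind it, and the present point makes no stated figure wrong.

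**Following one patient through the text.**

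| Situation | 2.1.2 | 4.2 | Counted for applicability? |
|---|---|---|---|
| No DP performed | Replaced | Not treated | No, and rightly so |
| DP done, no sealant applied | Replaced (any reason) | Not treated | No; this is the defect |
| DP done, application aborted or partial | Not stated whether it was performed | Not stated whether treated | Open |
| DP done, sealant applied with problems | Not replaced | Treated | Yes, with CRF description |

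**Size, by assumption.** The documents give no rate of failed application after DP, so the number of failures k is assumed. With 35 treated patients reached by replacement, the proportion among the treated is 35/35 whatever k is. With the failures kept, it is 35/(35 + k). The intervals are exact (Clopper–Pearson) 95% intervals with the total taken as fixed:

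| k assumed | Treated only | All intended applications |
|---|---|---|
| 0 | 35/35 = 100% (90.0–100) | 35/35 = 100% (90.0–100) |
| 1 | 100% (90.0–100) | 35/36 = 97.2% (85.5–99.9) |
| 3 | 100% (90.0–100) | 35/38 = 92.1% (78.6–98.3) |
| 5 | 100% (90.0–100) | 35/40 = 87.5% (73.2–95.8) |

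For 35/35 the lower limit is 0.025^(1/35) = 0.900.

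**How likely is at least one failure?** For an assumed true failure probability p, the chance of one or more in 35 patients is 1 − (1 − p)^35, and the expected number replaced before 35 are treated is 35p/(1 − p):

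| p assumed | Chance of at least one | Expected number replaced |
|---|---|---|
| 2% | 0.507 | 0.71 |
| 5% | 0.834 | 1.84 |
| 10% | 0.975 | 3.89 |

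Even a low failure rate gives a fair chance that the rule is used at least once.

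**The case against.** Several arguments on the other side are sound and limit the point.

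- **Partial exposure.** A reader might infer that patients with an aborted or partial application also leave the safety denominator. The text does not support this. Section 4.2 says that all treated patients are considered, and section 5.2 requires adverse events to be documented from application onwards. Nothing says that an exposed patient is dropped. What stands is that *treated* is not defined for an incomplete application.
- **Non-adherence.** Appendix II, section VIII lists "Failure of the sealant to adhere to the tissue" as a potential adverse effect of this class of sealant, and one might infer that such events would vanish. They need not: Visit 2 asks for application problems and names an adhesive that did not stick as an example, and the device log records units and deficiencies per patient. But these records describe events; neither puts a replaced patient into a denominator.
- **Status of applicability.** It is not a listed endpoint in section 2.3, and most statements about the next trial mention safety alone. So the plan does not announce a 100% feasibility figure. It remains true that applicability justifies the sample in sections 2.1.1 and 4.1, and that feasibility is a condition in section 4.2.
- **Failure counts.** They are assumptions. The nearest data in the document are vascular: in the pivotal study in Appendix II, all 101 patients randomised to this sealant were treated. That is 0/101 untreated, with an exact upper 95% limit of 1 − 0.025^(1/101) = 3.6%. The scenarios with 3 and 5 failures (3/38 = 7.9%, 5/40 = 12.5%) lie above it. A clamped vessel is a different site from a cut pancreas, so this does not settle the rate, but none of the lower percentages may be called the true one.
- **Left to an analysis plan.** Population details and patient-flow reporting often are, and replacement is not deletion. But replacement is a conduct rule fixed in the protocol. The protocol does not require the reason for a replacement to be recorded, and adverse event documentation does not begin in a patient who receives no sealant. A later plan could not be sure of recovering what was never collected.

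**Conclusion.** The point holds for patients with a completed DP in whom no sealant was applied. They are replaced under section 2.1.2 and lie outside the only population named in section 4.2, so the applied proportion among those analysed is 35/35 by construction. For aborted or partial applications the text leaves the matter open.

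Under assumed counts of 1 to 5 failures, the difference is between 100% and 97.2% to 87.5%. It is zero if no failure occurs. It rests on reading *intervention* as the sealant step (section 2.2.2) and on assumed counts.

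No listed primary endpoint, sample size or other stated figure becomes wrong. The weight is moderate: the rule biases the judgement of applicability and is easily corrected before enrolment, but it does not undermine the assessment of safety in exposed patients.

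**What to change.** **Section 2.1.2:** limit replacement to patients in whom no DP was performed or who withdrew before application was attempted. Record the reason for every replacement.

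**Section 4.2:**
- Use all patients with a DP and an intended application as the denominator for applicability.
- State that any sealant exposure, complete or not, counts as treated for safety and for pancreatic fistula.
- Report every replaced patient with the reason.

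The synopsis figures of 35 allocated and 30 analysed should be reconciled with the rule at the same time, since section 2.1.2 replaces such patients until the planned number is reached.

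**Cost:** a few sentences, one or a few extra patients followed, and possibly a lower feasibility figure. Because a failed application is no longer replaced, the exposed group may fall slightly short of 35. If 35 exposed patients are wanted, recruitment can continue to that number, provided the failures stay in the applicability denominator.
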